## Measures

Data will be collected via the Survey Solutions platform (World Bank, V.20.08, 2021). Study nurses enter data directly into electronic tablets with programmed validity checks during study visits. The tablets are regularly synchronised to a server on the ACIPH campus.

## MRI

MRI imaging protocol: MRI data collection will be performed by a trained radiography technologist using the portable, ultra-low field (0.064 Tesla) Hyperfine MRI system (Guilford, Connecticut, USA) installed at FHCSH. We will use the UNITY consortium common protocol which consists of volumetric T1 and T2-weighted imaging and quantitative T2 imaging, optimised for infant/paediatric brain (table 3).^12^ Magnetisation-prepared rapid gradient echo sequences will be used for volumetric T1 imaging, and turbo-spin echo acquisition will be used to attain T2-weighted images.

**Table 3 T3:** The main imaging protocol used in the UNITY studies for children older than 1 month

	Image matrix (X×Y×Z)	Resolution(X×Y×Z) mm^3^	TE/TR/TI (ms)	Time (min:s)
T2 FSE (axial)	112×136×40	1.5×1.5×5	180/2000/NA	2:15
T2 FSE (coronal)	112×44×124	1.5×1.5×5	220/2000/NA	2.22
T2 FSE (sagittal)	36×136×124	1.5×1.5×5	225/2000/NA	2:12
T1 IR-FSE (axial)	112×138×40	1.5×1.5×5	6.6/880/354	6:11
T2 Mapping (optional)	20×18×22	1.7×1.7×5	41, 81, 122, 163, 204, 244, 285, 326, 366, 407/2000/NA	9:22

FSEFast Spin EchoTEEcho timeTIInversion timeTRRepetition time

The protocol for the MRI study visit was developed based on formative work conducted before the study as part of the Longitudinal Infant Development and Growth (LIDG) study.^13^ During the scan, caregivers will be invited to stay in the scanning room to provide comfort and encouragement as needed. Appointments will be scheduled during nap times or when children are anticipated to be tired. Infants and young children will be fed, soothed to sleep and placed in the scanner. Older children who remain awake during the scan will be encouraged to lie still, and a tablet may be used immediately outside the scanner as a distraction. Earplugs will be placed prior to scanning to prevent startling or awakening during the scan. The sequences take around 35 min to complete. Scans will be repeated up to two times if movement or image artefacts are significant during live monitoring of the scan quality. A clinical read/interpretation of the MRI will be done by senior radiologists at FHCSH within 1 week of the scan. Incidental findings will be communicated to the family along with a plan for referral. The primary MRI outcome will be total supratentorial brain volume. We will also assess ventricular, Cerebrospinal Fluid (CSF), and thalamus volumes.

### Other measures

All children will undergo an anthropometric assessment and a cognitive developmental assessment. Children aged 6–36 months will complete the WHO Global Scales for Early Development (GSED) while children aged 48 and 60 months will complete a battery of tasks selected to assess different aspects of cognitive development, executive functions and self-regulation as well as a tool to assess early maths skills, literacy and knowledge as all of these domains are believed to reflect aspects of child-level school readiness. Tools were piloted in March 2024, and minor adaptations were made to be culturally relevant, feasible, acceptable and age appropriate.

#### Child anthropometrics assessment

Anthropometric assessments will be done at the enrolment visit using standard methods described by INTERGROWTH-21.^14^ Infant weight will be measured using a high-quality digital scale (ADE M112600, Germany; precision 5 g). Child weight will be measured with a high-quality digital scale (ADE M317600, Germany; precision 100 g). For infants under 24 months of age, we will measure recumbent length to the mm using a portable infantometer (Perspective Enterprises PE-RILB-LTWT, Michigan USA, precision 1 mm), which has a fixed headboard and movable footboard. For children aged 24 months and older, height will be measured using a high-quality adult stadiometer (Shorr Productions). Head and mid-upper arm circumferences will be measured to the nearest millimetre using insertion tapes (Shorr Productions). Regular calibration checks will be made to ensure the accuracy of the scales. Parameters will be measured in duplicate.

#### WHO Global Scales for Early Development

The Global Scales for Early Development (GSED) was developed by a team assembled by the World Health Organization (WHO) to assess global child development across cultures and settings in children aged 0–36 months of age and will be used to assess child development in children aged 6–36 months.^15^ The GSED assesses development across multiple domains including cognition, motor, language and socioemotional development. We will use both the short form, a caregiver report and the long form, a direct assessment which can be used to derive a global D-score for overall child development. The GSED has been validated in Tanzania, Bangladesh and Pakistan,^16^ and more validations are underway.^17^ We worked with WHO to translate, culturally adapt and field-test the instruments for the Ethiopian context. The adaptation process followed a process whereby it was translated into Amharic language by two independent early childhood experts who held a consensus meeting with local early child development field experts to make sure the tool was culturally appropriate. These adaptations were then back-translated, then approved by WHO and piloted. Two Ethiopian master trainers (KY and AT) were trained by WHO and trained a team of local study nurses. The GSED takes about 1 hour to administer and uses the Open Data Kit platform.

#### Visual reasoning, verbal expression and school readiness

We will use paper-based tasks to assess visual reasoning, verbal expression and school readiness in children aged 48–60 months. These domains were selected as important to school readiness as reflecting preacademic knowledge and mental flexibility and preparedness to learn. These tasks were also selected because they had been used previously with children in a similar age range in Bahir Dar.^18^ We did further piloting and made minor adaptations based on feedback from children and experts during prestudy piloting. Changes concerned drawn images that the child did not recognise; for example, for a lake picture, we selected higher quality more recognisable images. These tasks take about 15 min to complete.

Visual matrix reasoning: Children will be shown stimuli in a booklet containing matrix diagrams and asked to choose an image they think will complete a sequence of 4–5 images. The task has 3 practice items and 29 test items. The complexity of the task increases as the task progresses.

Verbal expression: An assessor will read a sentence similar to ‘X and Y are both …’, X and Y being two objects or phenomena that represent a shared category. The child completes the sentence by stating what X and Y both represent, for example, ‘blue and green are both colours’. The task has 3 practice items and 20 test items. Concepts increase in complexity as the task progresses. The child’s verbatim response is written down for each item.

School readiness: A battery of verbal and paper and pen-based tasks that test concepts relevant to early knowledge formation and important skills for success in school, including knowledge of literacy, numeracy, early reading, crystallised knowledge and working memory will be used to assess preacademic knowledge.

#### Executive functions

Executive functions will be assessed in children ages 4–5 using three tasks from the National Institute of Health (NIH) Toolbox listed below. Tasks were selected to reflect different aspects of executive functions such as attention, inhibitory control and processing speed which we believe are important for learning and readiness for school. The NIH Toolbox App is administered on an iPad (iOS 16) and the assessment time is around 20 min. Computer-generated scores reflect accuracy and reaction time metrics.^19^ Children are asked to go as fast as they can without making mistakes.

Dimensional Change Card Sort (DCCS): DCCS measures cognitive flexibility and attention. Children are shown figures (stimuli) that vary across two dimensions, shape and colour. The child is asked to select one of two stimuli that best match a central target stimulus based on one characteristic (shape or colour). Children practise matching based on colour and shape before the actual trial items

Flanker Inhibitory Control and Attention Task: The Flanker Task measures inhibitory control and attention. Children are presented with a row of fish and/or arrows and have to select a response button that shows the direction of the central stimulus (fish or arrow) by pressing one of two buttons on the screen.

Speeded matching: The Speed matching task assesses processing speed. Children are asked to identify which of four targets (pictures of two-dimensional animal faces) match the target picture at the top of the screen by tapping an image as quickly as possible without making mistakes. The task starts with four practice items with feedback. The trial finished after 90 s.

#### Self-regulation

In addition to cognitive skills and early knowledge, self-regulation is an important aspect of school readiness as it helps children learn and thrive in a classroom setting and in social interactions. Study nurses will complete a brief survey assessing the child’s observed self-regulation skills in children aged 48–60 months. This survey was adapted from items from The International Development and Early Learning Assessment (IDELA)^20^ and the Preschool Self-Regulation Assessment^21^ to be culturally relevant and age appropriate. It assesses behaviours such as attention, confidence in own abilities, diligence, frustration and positive mood. The eight items are scored on a 4-point Likert scale and summed to create a total score.

#### Surveys

Surveys completed by the mother at the enrolment visit are listed in box 1.

Box 1Outcome measuresPrimary outcomeTotal supratentorial brain volume.Secondary outcomesGlobal child development (Global Scale for Early Development scores) (6–36 months).Cognitive functioning (48–60 months).School readiness (48–60 months).Executive functioning (48–60 months).Self-regulation (48–60 months).Surveys on key exposures (assessed by maternal self-report)Maternal education, occupation, self-reported ranking of socioeconomic status and a list of assets and housing conditions used to create a socioeconomic index.Maternal depression and perceived stress are assessed using the 9-item Patient Health Questionnaire and the 10-item Cohen’s Perceived Stress Scale, both of which were previously validated in Ethiopia.^22^Child health and morbidity questions include reports of birth complications, hospitalisations since birth, serious medical conditions, chronic conditions and acute illness in the last 12 months including febrile illness, diarrhoea, malaria, respiratory illness and child emotional well-being (eg, depression/tearfulness, fears and easily scared).Childhood Adversity Index assesses using 13 items adapted from the Daily Hardships Survey.Child diet questionnaires, including breastfeeding history, dietary diversity, nutrient intake from 7-day semiquantitative food frequency questionnaires, food insecurity.Parenting/family environment (caregiver engagement in stimulating activities and learning materials in the home assessed using items from the UNICEF Multiple Cluster Indicator Survey).Other exposures (measured by research staff)Anthropometrics (height-for-age, weight-for-age and weight-for-height).Child haemoglobin/anaemia (measured at study visit).

### Quality control

Quality assurance checklists will ensure that measurements meet a minimal standard. Staff will be observed and required to achieve competency before conducting neurobehavioural and developmental assessments. We will monitor the quality of data by reviewing 10% video-recorded assessments of the GSED assessments. MRI will be reviewed by the MRI technician during acquisition and further reviewed by local radiologists and researchers at Brown University for quality control and to provide feedback to the MRI technician.

## Analysis

### Statistical analysis

Descriptive statistics (eg, means and SD, frequencies, and percentages) for key variables will be examined for each cohort. We will use a linear regression approach to estimate associations between exposures and continuous outcomes overall and by cohort. Regression assumptions will be checked and methods such as natural log (ln) transformation may be used to meet normality assumptions. Where appropriate, we will standardise data using relevant reference samples or z-scores created within the sample. We will account for key confounders using a multivariable approach. Baseline characteristics associated with both the outcome and exposure status (p<0.10) will be included in adjusted models as potential confounders.

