## Methods and analysis

### Study design

The BCD Cohort is a cross-sectional observational study designed to characterise typical neurodevelopment in the first 5 years of life in Bahir Dar, Ethiopia.

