### Study participants and recruitment

The BCD study will enrol healthy children from age 6 to 60 months across eight age cohorts (see table 1). Eligible children will be identified during routine outpatient and vaccination visits at the study health centres. Children who present with clinical symptoms based on parental/child self-report will not be eligible to participate. We will aim to recruit N=50 children into each cohort of the eight cohorts for a total cross-sectional sample size of N=400. Inclusion and exclusion criteria and additional MRI screening questions are shown in table 2.

**Table 1 T1:** Overview of data collection across the cross-sectional cohorts (A–H)

	Enrolment visit		MRI visit
**Cohort**	Assessments	Surveys	Assessments
A/6 monthsB/12 monthsC/18 monthsD/24 monthsE/30 monthsF/36 months	GSED long form (secondary outcome) GSED short form (secondary outcome) Anthropometrics Haemoglobin	Sociodemographic information Home environment Parenting Health history	MRI (Primary outcome)
G/48 monthsH/60 months	Neurocognitive development assessment of reasoning and verbal expression (secondary outcome) Executive functioning (secondary outcome) School readiness (secondary outcome) Anthropometrics Haemoglobin [figure not shown]	Sociodemographic information Home environment Parenting Health history [figure not shown]	MRI (Primary outcome) [figure not shown]

GSEDGlobal Scale for Early Development

**Table 2 T2:** Inclusion and Exclusion criteria

Inclusion criteria	Exclusion criteria
Child lives in Bahir Dar with parents who are willing to travel to FHCSH clinic for the MRI. Family has no plans to move outside of the catchment area in the next 6 months Child is healthy without active clinical symptoms/complaints. The child is within specified age bins for one of the cohort/group±1 months for the 6, 12 and 18 months old and ±2 months for the 24, 36, 48 and 60 months old children.	Child was born with a congenital birth defect or hypoxic ischaemic encephalopathy (birth asphyxia) per maternal report. Child has developmental delay or behavioural disorder per maternal report. Child has clinical signs or symptoms of illness based on maternal and child report (including vomiting, headache or seizures).
Additional screening for MRI scanning	
	Surgical hardware such as staples or screws Metal shrapnel or bullets; Suspected metal in eye; metal jewellery or watch; Metal-containing tattoos or permanent make-up on head or neck.

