### Sample size calculation

The sample size of n=50 children per cohort was selected to ensure collection of at least 30 high-quality MRI per cohort. Expected reasons for data loss include loss to follow-up since MRI is collected during a second visit and poor quality of the images due to movement artefact or incomplete brain visualisation. MRI is an objective quantitative measure; this sample size is widely considered adequate to establish normal population distributions (mean, SD) of brain parameters and brain volumes.^11^

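### The p<0.10 double screen for confounders is unreliable if applied within cohorts and cannot tell a confounder from a mediator, so adjusted associations can be biased

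*Protocol article*

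**What the plan says.** The Statistical analysis section of the protocol article states an intention and then a rule. The intention is "We will account for key confounders using a multivariable approach"; no confounder is named. The rule is "Baseline characteristics associated with both the outcome and exposure status (p<0.10) will be included in adjusted models as potential confounders". The regressions are meant to "estimate associations between exposures and continuous outcomes overall and by cohort". The article does not say whether the screen is run once on the pooled sample or again in each cohort, and it does not define which variables are baseline characteristics.

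On numbers, Study participants and recruitment says "We will aim to recruit N=50 children into each cohort of the eight cohorts for a total cross-sectional sample size of N=400". Under Sample size calculation, the 50 per cohort was "selected to ensure collection of at least 30 high-quality MRI per cohort".

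On the variables, the study is cross-sectional, and anthropometry, haemoglobin and the surveys are all taken at the enrolment visit. Box 1 (Surveys) places "Anthropometrics (height-for-age, weight-for-age and weight-for-height" and haemoglobin among the other exposures, and diet and child illness among the key exposures. The Conclusions list poverty, food insecurity and stunted growth side by side as risk factors, without a causal order.

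**The concern.** A covariate enters the adjusted model only if it passes two significance tests in the same data. This raises two separate problems.

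- **Omission in small samples.** With 30 to 50 children, a test at p<0.10 has limited power for a moderate correlation, and the covariate must pass twice. True confounders can be dropped by chance, and different ones in different cohorts. A difference between age groups could then reflect adjustment rather than age, although the Introduction sets out to explore the relationships across age groups.
- **Blindness to causal role.** A mediator is associated with both exposure and outcome, so it meets the criterion as well as a confounder does. When the exposure is socioeconomic status, food insecurity or hardship, nothing in the rule keeps out height-for-age, haemoglobin, diet or illness. Adjusting for these removes part of the total association.

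The second goal in the Introduction is to relate risk and protective factors to neurodevelopment, and the article hopes to identify targetable factors. Both depend on knowing what each adjusted coefficient has been adjusted for.

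**Working it through.** **Inputs from the article.** 8 cohorts × 50 = 400, which matches the stated total. At least 30 usable MRIs per cohort gives 8 × 30 = 240 pooled, a yield of 30/50 = 60%. The screening level is 0.10, taken as two-sided because sidedness is not stated.

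**Assumed inputs.** The correlation r of a confounder with the exposure and with the outcome is not given. It is varied below.

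**Step 1: chance that a confounder passes both tests.** By the Fisher z approximation, the power of one test is Φ(atanh(r)·√(n−3) − 1.645). Treating the two tests as roughly independent, this is squared. For n=30 and r=0.3: 0.3095 × √27 − 1.645 = −0.04, power 0.485, squared 0.24.

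| r | n=30 | n=50 | n=240 |
|---|---|---|---|
| 0.2 | 8% | 16% | 87% |
| 0.3 | 24% | 47% | 99.8% |
| 0.4 | 51% | 80% | about 100% |
| 0.5 | 79% | 97% | about 100% |

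Simulation, which does not need the independence approximation, gives omission of about 75% (n=30) and 52% (n=50) at r=0.3, and about 45% and 18% at r=0.4. The screen misses a confounder more often than not when r is below about 0.40 at n=30, 0.31 at n=50 and 0.14 at n=240.

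**Step 2: what omission does to the estimate.** Simulation with true effect zero: screen each confounder, then fit ordinary least squares. Bias is in SD of outcome per SD of exposure.

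| Independent confounders | Bias, n=30 / n=50 | Type I error, n=30 / n=50 |
|---|---|---|
| one at r=0.3 | 0.04 / 0.02 | near 5% / near 5% |
| two at r=0.3 | 0.08 / 0.05 | about 7% / 6% |
| four at r=0.2 | about 0.10 / 0.09 | about 7% / 8-9% |
| four at r=0.3 | 0.18 / 0.13 | about 15% / 14% |

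Fixed adjustment for all the confounders gives bias of about 0 and type I error of about 5% in these settings. At n=240 and r=0.3, screened and fixed adjustment agree.

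**Step 3: mediators.** With an exposure-to-mediator path a, a mediator-to-outcome path b and a direct effect d, the total is d + ab, and adjusting for the mediator removes ab. Taking a = b = 0.3 and d = 0.2, the total is 0.29 and 0.09 is removed (0.09/0.29 = 31%). The screen admits this mediator in 36% of samples at n=30, 60% at n=50 and about 100% at n=240. Mean bias against the total is −0.060, −0.072 and −0.090. With a = b = 0.4, the product is 0.16. Pooling therefore cures omission but makes admission of a mediator near-certain.

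**The case against.** The case on the other side has real force on several points.

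- **Strength of confounding.** A reader might infer that the screen misses most real confounders at these sample sizes. That holds only for weak to moderate ones. At r=0.4 about 45% (n=30) or 18% (n=50) are missed, and at n=50 and r=0.3 it is about half. The 15% type I error needs four independent confounders that together explain 4 × 0.3² = 36% of the variance of both exposure and outcome. Nothing in the article supports that as the expected case.
- **Level of screening.** The article runs models overall and by cohort but does not say that selection is repeated by cohort. A single selection on the pooled sample fits the text equally well, and omission at r=0.3 would then be negligible.
- **Mediators.** A reader might infer that stunting and haemoglobin will be adjusted for. The article lists them as exposures and leaves baseline characteristics undefined, so their entry is permitted, not stated. Their adjustment is a bias only for a total association, and the article does not specify total or direct effects.
- **Comparison with other countries.** Harmonised data can be reanalysed with a common model whatever this study adjusted for, so a claim of non-comparability is not supported.
- **The main aim.** The article says "The BCD Cohort is a cross-sectional observational study designed to characterise typical neurodevelopment", and the sample size is justified by means and SDs of brain volumes. Those descriptive results are untouched.

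These points narrow the concern without removing it. The rule is stated in the article, so it is not a detail left to an analysis plan, and it permits both failures.

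**Conclusion.** The concern holds in limited form. If the screen is applied within cohorts, it drops a confounder correlated 0.3 with both variables in about 75% (n=30) or 52% (n=50) of samples. The resulting bias with no true effect ranges from about 0.02-0.04 SD with type I error near 5%, through about 0.09-0.11 SD and 7-9%, to about 0.13-0.18 SD and 15%, depending on how many confounders there are and how strong. In the pooled MRI sample, omission at r=0.3 is negligible and the remaining weakness is that mediators pass the screen.

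Adjusted associations can therefore be biased, and adjustment sets may differ between cohorts. The stronger statement, that they are biased, would need confounder strengths, a per-cohort screen and a list of eligible covariates, none of which the article gives. The sizes rest on assumed correlations, normally distributed variables, independent confounders and a two-sided screen. The rule should be changed before analysis. It does not threaten the descriptive aim and requires no new data.

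**What to change.** Replace the screening sentence in Statistical analysis with an adjustment set for each exposure, chosen on subject-matter grounds before analysis and used unchanged in the overall model and in every cohort.

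- Include child age and sex, and recruitment site where it applies (some children come through community outreach).
- Include socioeconomic variables only where they are not the exposure, part of it or downstream of it. A blanket rule to adjust for the asset-based index would repeat the mediator problem when, for example, maternal education is the exposure.
- State that anthropometrics, haemoglobin, diet and child illness are not adjusted for in the main model when the exposure lies upstream of them. Report any such adjustment as a separate, secondary model.

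This is one paragraph of text. The cost is a few degrees of freedom per model, which matters most at n=30: an exposure plus five covariate terms and an intercept leaves 30 − 7 = 23 residual degrees of freedom, so the set should be kept short. The choice must be made before the data are analysed, because a set chosen afterwards is not pre-specified.
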